## Abstract

**Background:**

The management of small gastric submucosal tumors (SMTs) originating from the muscularis propria layer (SMT-MPs) remains a subject of debate. Endoscopic submucosal dissection (ESD) is currently considered the optimal treatment for resection. However, high expenses, complex procedures, and the risk of complications have limited its application. Our previously proposed novel operation, precutting endoscopic band ligation (precutting EBL), has been demonstrated in a long-term, single-arm study to be an effective and safe technique for removing small gastric SMTs. However, the absence of a pathological examination and the potential for delayed perforation have raised concerns. Thus, we modified the precutting EBL by adding endoscopic resection to the snare after ligation and closure, yielding the precutting endoscopic band ligation-assisted resection (precutting EBLR). Moreover, the initial pilot study confirmed the safety and efficacy of the proposed approach and we planned a randomized controlled trial (RCT) to further validate its clinical feasibility.

**Methods:**

This was a prospective, single-center, open-label, parallel group, and randomized controlled trial. Approximately 40 patients with SMT-MPs will be included in this trial. The patients included were allocated to two groups: ESD and precutting EBLR. The basic clinical data of the patients were collected in detail. To better quantify the difference between ESD and precutting EBLR, the primary outcome was set as the operation duration. The secondary outcomes included total operation cost and hospitalization, intraoperative adverse events, and postoperative recurrence. The primary outcome was tested for superiority, while the secondary outcomes were tested for noninferiority. SPSS is commonly used for statistical analysis.

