Endoscopic resection, in comparison to open or laparoscopic surgery, yields a shorter operation duration, reduced blood loss, and shorter average hospitalization duration [9–14]. Endoscopic submucosal resection (ESD) has been demonstrated to be feasible for treating gastric SMTs. Guidelines from the European Society of Gastrointestinal Endoscopy (ESGE) and the American Society for Gastrointestinal Endoscopy (ASGE) recommend ESD as the preferred treatment for most gastric superficial neoplastic lesions [15, 16]. However, its effectiveness is limited for lesions originating from deeper layers such as the muscularis propria, increasing the complexity of the operation and the risk of complications. A systematic review by Ichiro Oda et al., encompassing more than 300 patients with early gastric cancer treated with ESD, identified several complications associated with the procedure. These complications included perforation (1.2–5.2%), bleeding (7% for immediate bleeding, up to 15.6% for delayed bleeding), stenosis (0.7–1.9%), aspiration pneumonia (0.8–1.6%), and air embolism, among others [17]. Although management strategies exist for these adverse events, they demand a higher level of technical expertise, adding to the financial burden and psychological stress on patients. Furthermore, ESD may not always achieve R0 resection, posing challenges for diagnosis and prognosis [18, 19]. According to an analysis of 733 patients with upper gastrointestinal SMT-MPs, extensive tumor connection was identified as a risk factor for incomplete resection [20]. In a multicenter prospective study by Ye LP et al. involving 692 patients, the R0 resection rate was 84.2% [19]. Hence, a more judicious treatment approach is imperative.

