We previously introduced a novel endoscopic treatment termed precutting EBL. In this operation, an electrosurgical snare resection is performed to initially remove the mucosa surrounding the tumor, followed by the use of a transparent ligator to suction the tumor. A long-term, single-center study has substantiated its safety and efficacy. Precutting EBL was associated with a significantly shorter operation duration (16.6 min) and lower cost ($603.3 ± 5.9) than ESD ($2783 ± 601), and it was associated with fewer complications [21]. However, precutting EBL has two notable drawbacks. First, pathological specimens were not collected since the tumor spontaneously drops off after ligation, necessitating long-term follow-up for eradication verification. Second, like other ligate-and-let-go techniques, there is a risk of delayed perforation after the operation, which warrants careful consideration [22]. Given that we did not have sufficient samples to assess the possibility of delayed perforation, we opted to perform en bloc resection of lesions after ligation. Although this approach increases the chances of intraoperative perforation, we can promptly address this possibility if it occurs. Consequently, we propose a modified endoscopic operation for small gastric SMT-MPs, termed precutting EBLR. This involves an additional snare resection immediately after ligation. After thorough communication and detailed informed consent, we experimentally performed precutting EBLR on 16 patients. All patients showed rapid postoperative recovery, with no instances of delayed gastric bleeding or perforation. Importantly, subsequent pathological examination confirmed R0 resection in every patient.

To further enhance the clinical validation of precutting EBLR, we opted to initiate a randomized controlled trial comparing the efficacy and safety of ESD and precutting EBLR for the treatment of small gastric SMT-MPs.

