### Outcomes and follow-up

The primary outcome for the trial was operation duration, and the secondary outcome was operation cost. Both outcomes will be assessed prior to discharge. Additional meaningful indicators, also set as secondary outcomes, include estimated blood loss, intraoperative and postoperative adverse events (such as bleeding, immediate and delayed perforation, infection), tumor recurrence, mortality rates, and hospitalization costs.

The trial’s endpoint will be established as 6 months after the operation of the last included patient. Each patient is given a detailed follow-up evaluation via telephone 6 months after discharge to gather information about their postoperative condition. At the 6-month mark, patients are required to undergo an endoscopic re-examination to assess tumor recurrence.

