^a^Specimens’ sizes were measured by rulers after resections

The primary outcome was set as the operation duration, with the objective of showcasing the main advantage of precutting EBLR. The other outcomes also help to demonstrate the safety and efficacy of the treatment, such as reduced hospitalization costs when the duration is equal or shorter hospitalization duration when the costs are equal. Precutting EBLR holds the potential to emerge as a creative and promising endoscopic approach for treating SMT-MPs, offering a more practical, simpler, and safer alternative. Moreover, this approach has the potential to alleviate the economic burden on both patients and health insurance companies, leading to substantial societal benefits. These advantages also foster the prospect of transforming the resection of gastric small SMT-MPs from a hospitalized operation to an ambulatory operation.

This trial has several limitations. The relatively small sample size may introduce bias if patients are lost to follow-up, and conducting further multicenter studies could address this issue. Additionally, the 6-month follow-up duration might be insufficient to thoroughly observe tumor recurrence. Currently, there is a lack of a specific method for investigating tumor recurrence in a timely manner. In other words, if tumor recurrence occurs at 1 or 6 months after the operation, it is ultimately identified during the re-examination 6 months after discharge. This may lead to an underestimation of the impact of different operations on tumor recurrence.

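### Noninferiority is stated for intraoperative adverse events, but on the only figures given it is implausible for immediate perforation; report the difference with its confidence interval and base the safety conclusion on that

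*Protocol article*

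**What the plan says.** All references are to the Protocol article.

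- **Abstract, Methods.** The outcome list reads "The secondary outcomes included total operation cost and hospitalization, intraoperative adverse events, and postoperative recurrence". The next sentence sets the hypotheses: "The primary outcome was tested for superiority, while the secondary outcomes were tested for noninferiority".
- **Outcomes and follow-up.** The adverse events are "intraoperative and postoperative adverse events (such as bleeding, immediate and delayed perforation, infection", so immediate perforation belongs to the set tested for noninferiority.
- **Discussion, Table 2.** Intraoperative perforation occurred in 10 of the 16 pilot patients treated with precutting EBLR, printed as 68.8%. It has its own row, above and separate from the rows headed as adverse events, all of which are zero.
- **Interventions, Precutting EBLR.** Closing the perforation caused by ligation is described as a step of the procedure.
- **Background and rationale.** The only ESD perforation rate appears here: "These complications included perforation (1.2–5.2" percent, from a review "encompassing more than 300 patients with early gastric cancer treated with ESD". The same paragraph says complication risk with ESD rises for lesions of the muscularis propria, but gives no rate for them.
- **Statistical analysis.** Categorical data are given as numbers and percentages and compared by Fisher's exact or chi-square test.
- **Discussion.** Precutting EBLR is said to have the potential to become a new approach "offering a more practical, simpler, and safer alternative".

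**The concern.** A noninferiority objective presumes that the new procedure is, at worst, slightly less good than the control. For immediate perforation, the event rate in the authors' own pilot lies far above the only ESD rate they cite. If that gap carries into the trial, the stated objective is out of reach. The likely finding would then be a trade: a shorter operation against more intraoperative perforation.

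The test named for categorical data adds a second risk. A nonsignificant Fisher or chi-square result in 40 patients could be read as noninferiority although the excess is large. Either way, the safety statement placed beside the operation-duration result would not describe what the trial measured.

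**Working it through.** **Inputs**

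- Precutting EBLR: 10 of 16 (Discussion, Table 2).
- ESD: 1.2–5.2% (Background and rationale). Rates of 20% and 30% are assumptions, used because no rate for muscularis propria tumors is given.
- 20 patients per arm (Allocation).
- Margin: the article shows none, so 30 points is assumed as a generous value. Noninferiority is taken as shown when the upper limit of the two-sided 95% Newcombe interval for the difference (EBLR minus ESD) is below 0.30.

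**Step 1. The printed pilot figure.** 10/16 = 62.5% and 11/16 = 68.8%, so the count and the percentage in Table 2 disagree. The exact (Clopper-Pearson) 95% CI for 10/16 is 35.4% to 84.8%.

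**Step 2. Gap on the figures given.** 62.5 − 5.2 = 57.3 points and 62.5 − 1.2 = 61.3 points. At the pilot's lower limit, 35.4 − 5.2 = 30.2 points. If the true EBLR rate were 5.2%, 10 or more events in 16 patients would have probability of about 9 × 10⁻¹⁰.

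**Step 3. What would make the hypothesis true.** With EBLR at 62.5%, the ESD rate would have to exceed 62.5 − 30 = 32.5% for a 30-point margin, 42.5% for 20 points, or 52.5% for 10 points.

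**Step 4. Chance of each result with 20 per arm.** Sum the binomial probabilities P(a; 20, p_EBLR) × P(b; 20, p_ESD) over all outcome pairs (a, b) that meet the criterion:

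| EBLR v ESD | Noninferiority shown (30 points) | Fisher P < 0.05 favouring ESD |
|---|---|---|
| 62.5% v 5.2% | 0.00003 | 98% |
| 62.5% v 20% (assumed) | 0.3% | 71% |
| 62.5% v 30% (assumed) | 2.4% | 41% |
| 35.4% v 5.2% | 2.4% | 59% |
| 35.4% v 20% (assumed) | 22% | 12% |
| 35.4% v 30% (assumed) | 44% | 3% |

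**Step 5. Can the named test support noninferiority?** At 62.5% v 30%, Fisher's test is nonsignificant in 59% of trials, although the true excess is 32.5 points. For example, take 12 of 20 against 6 of 20:

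- Fisher's P = 0.11.
- The Wilson intervals are 0.387–0.781 and 0.145–0.519.
- Newcombe upper limit: 0.30 + √[(0.781 − 0.600)² + (0.300 − 0.145)²] = 0.54.
- Newcombe lower limit: 0.30 − √[(0.600 − 0.387)² + (0.519 − 0.300)²] = −0.01.

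The P value says no difference was shown. The interval says that an excess of up to 54 points is compatible with the data.

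**The case against.** Several objections have force.

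**The expected increase is not against ESD.** A reader might infer that the plan itself predicts more perforation than with ESD, because it says "Although this approach increases the chances of intraoperative perforation, we can promptly address this possibility if it occurs". That sentence follows "we opted to perform en bloc resection of lesions after ligation" and compares the modified technique with precutting EBL, where the ligated tumor is left to fall off. It is no evidence about the randomized comparison, and nothing above relies on it.

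**The hypothesis is not shown to be false.** A reader might also infer that noninferiority is contradicted outright, or almost sure to fail. The pilot had 16 patients and no control arm, the ESD rate comes from another disease, and the article itself says the risk is higher in deeper lesions. At 35.4% v 30% the chance of success is 44%. Sample size also plays a part: with equal rates of 62.5% in both arms, noninferiority at 30 points would be shown only 57% of the time. These points stand and limit the conclusion to implausibility on the figures given.

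**Perforation is not the whole outcome.** The abstract names intraoperative adverse events overall, which include bleeding. The calculation covers immediate perforation alone. Table 2 and the procedure description suggest that a closed perforation might not be counted, while Outcomes and follow-up counts it. This stands as a conflict to reconcile.

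**The safety wording is only an outlook.** The Discussion gives *safer* as a potential, not as a hypothesis or decision rule, so it should not be called a planned conclusion.

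**Rates by arm are already planned, and an unfavourable test is a legitimate result.** Numbers and percentages are indeed specified, and taking perforation out of scrutiny because the new arm may do badly would be wrong. For that reason the event should stay a reported adverse event in both arms.

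**Conclusion.** The point holds in limited form. Noninferiority on immediate perforation is implausible on the only figures the article gives: a gap of 57 to 61 points at the pilot estimate, and a chance of about 0.00003 of showing it at a 30-point margin with 62.5% v 5.2%. With the assumed ESD rates and the pilot's lower confidence limit, the chance ranges from 0.3% to 44%. The size therefore depends on the unknown ESD rate in muscularis propria tumors, the wide pilot interval and the assumed margin.

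The conclusion about the test depends less on those inputs. A nonsignificant Fisher or chi-square result cannot establish noninferiority, and it is likely (59%) even with a true excess of 32.5 points. Even a successful noninferiority result would not by itself show that precutting EBLR is safer. The misprinted percentage in Table 2 is a clerical side point.

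**What to change.** 1. Do not rest the safety conclusion on noninferiority for immediate perforation.
2. Keep it as a reported adverse event in both arms, as Outcomes and follow-up has it. Reconcile that section with Table 2, which lists it outside the adverse events, and with the Precutting EBLR section, which treats its closure as a procedural step.
3. Report each arm's rate and the difference with a 95% confidence interval beside the operation-duration result, so that time saved and perforation can be read together.
4. Word the safety conclusion from that estimate, and use *safer* only if the estimate supports it.
5. Make the pilot count and percentage in Table 2 agree after checking the source.

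The cost is wording and one confidence interval. Sample size, procedures and data collection do not change. The downside is a less favourable stated safety objective.

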**Discussion:**

This study was designed to validate the feasibility of a novel operation for removing gastric SMT-MPs. To intuitively assess this phenomenon, the operation durations of precutting EBLR and ESD were compared, and other outcomes were also recorded comprehensively.

**Trial registration:**

Chinese Clinical Trial Registry ChiCTR2200065473. Registered on November 5, 2022.

**Supplementary Information:**

The online version contains supplementary material available at 10.1186/s13063-024-07902-7.

## Introduction

### Background and rationale

Submucosal tumors (SMTs) histologically include both epithelial and nonepithelial tumors. Nonepithelial tumors typically present as protruding lesions or masses covered with intact mucosa [1]. Large SMTs (≥2 cm) in the stomach may lead to early-stage complications such as bleeding or perforation, resulting in symptoms such as abdominal bloating, pain, hematemesis, or melena, which prompt patients to seek medical attention. In contrast, small gastric SMTs (<2 cm) are typically discovered incidentally during endoscopy without any apparent symptoms [2, 3].

The risk of small gastric SMT-MPs has been underestimated [4]. Studies suggest that 60–70% of SMT-MPs are pathologically identified as gastrointestinal stromal tumors (GISTs) and categorized as potential malignancies regardless of their size [2, 3]. However, although surgeons propose resection for large gastric SMT-MPs, clinical controversy persists [1, 5, 6]. In a retrospective study conducted by Ge QC et al. [7], a cutoff value of 1.48 cm was established to predict the malignant potential of GISTs. Tumors larger than 1.48 cm were associated with greater malignant potential, warranting intensive surveillance or endoscopic surgery. According to the modified National Institute of Health, the risk of small GISTs varies only with the mitotic count. The classifications included very-low risk (mitotic count ≤5), intermediate risk (mitotic count between 5 and 10), and high risk (mitotic count >10). Some advocate for imaging surveillance as the primary approach, suggesting resection only when tumor progression is confirmed. This includes cases where the tumor shows signs of increasing size, irregular borders, or pathological confirmation as a cancer [8]. Although endoscopic ultrasound (EUS) is a common method for diagnosing gastrointestinal superficial lesions, its role in diagnosing SMT-MPs has not been determined. Additionally, consistent observation of dynamic changes in tumor size and border length for patients with SMT-MPs < 16 mm is challenging. Although EUS-guided fine needle aspiration (EUS-FNA) is often employed for pathology, it may not fully reveal the pathological features of GISTs due to heterogeneity. In conclusion, en bloc resection is crucial for both diagnosis and prognosis [9].

Endoscopic resection, in comparison to open or laparoscopic surgery, yields a shorter operation duration, reduced blood loss, and shorter average hospitalization duration [9–14]. Endoscopic submucosal resection (ESD) has been demonstrated to be feasible for treating gastric SMTs. Guidelines from the European Society of Gastrointestinal Endoscopy (ESGE) and the American Society for Gastrointestinal Endoscopy (ASGE) recommend ESD as the preferred treatment for most gastric superficial neoplastic lesions [15, 16]. However, its effectiveness is limited for lesions originating from deeper layers such as the muscularis propria, increasing the complexity of the operation and the risk of complications. A systematic review by Ichiro Oda et al., encompassing more than 300 patients with early gastric cancer treated with ESD, identified several complications associated with the procedure. These complications included perforation (1.2–5.2%), bleeding (7% for immediate bleeding, up to 15.6% for delayed bleeding), stenosis (0.7–1.9%), aspiration pneumonia (0.8–1.6%), and air embolism, among others [17]. Although management strategies exist for these adverse events, they demand a higher level of technical expertise, adding to the financial burden and psychological stress on patients. Furthermore, ESD may not always achieve R0 resection, posing challenges for diagnosis and prognosis [18, 19]. According to an analysis of 733 patients with upper gastrointestinal SMT-MPs, extensive tumor connection was identified as a risk factor for incomplete resection [20]. In a multicenter prospective study by Ye LP et al. involving 692 patients, the R0 resection rate was 84.2% [19]. Hence, a more judicious treatment approach is imperative.

We previously introduced a novel endoscopic treatment termed precutting EBL. In this operation, an electrosurgical snare resection is performed to initially remove the mucosa surrounding the tumor, followed by the use of a transparent ligator to suction the tumor. A long-term, single-center study has substantiated its safety and efficacy. Precutting EBL was associated with a significantly shorter operation duration (16.6 min) and lower cost ($603.3 ± 5.9) than ESD ($2783 ± 601), and it was associated with fewer complications [21]. However, precutting EBL has two notable drawbacks. First, pathological specimens were not collected since the tumor spontaneously drops off after ligation, necessitating long-term follow-up for eradication verification. Second, like other ligate-and-let-go techniques, there is a risk of delayed perforation after the operation, which warrants careful consideration [22]. Given that we did not have sufficient samples to assess the possibility of delayed perforation, we opted to perform en bloc resection of lesions after ligation. Although this approach increases the chances of intraoperative perforation, we can promptly address this possibility if it occurs. Consequently, we propose a modified endoscopic operation for small gastric SMT-MPs, termed precutting EBLR. This involves an additional snare resection immediately after ligation. After thorough communication and detailed informed consent, we experimentally performed precutting EBLR on 16 patients. All patients showed rapid postoperative recovery, with no instances of delayed gastric bleeding or perforation. Importantly, subsequent pathological examination confirmed R0 resection in every patient.

To further enhance the clinical validation of precutting EBLR, we opted to initiate a randomized controlled trial comparing the efficacy and safety of ESD and precutting EBLR for the treatment of small gastric SMT-MPs.

### Trial design and objective

This was a single-center, open-label, parallel-group, randomized controlled trial. The main objective of this trial was to verify the efficacy and safety of precutting EBLR in the management of small gastric SMT-MPs. The trial began on December 1, 2022. The procedures included recruitment, informed consent, allocation of participants, intervention, data collection, data monitoring, and statistical analysis. All procedures were conducted at The First Affiliated Hospital of Chongqing Medical University (CQMU). A detailed flowchart for this trial is available in the Supplementary Materials. The drafting of this manuscript adheres to the SPIRIT reporting guidelines [23]. The SPIRIT checklist is attached as Additional file 2 in Supplementary Materials.

